### Secondary outcomes

In women with FH compared with women without hypercholesterolaemia, we will investigate

The association between breastfeeding (yes/no, exclusive/partial, frequency and duration) and additional markers for ASCVD risk, eg,Inflammatory markers (eg, C-reactive protein (CRP)Metabolic markers (eg, glucose)WeightMeasurements will be performed in both plasma/serum and in peripheral blood mononuclear cells (PBMCs) (gene expression levels).The breast milk composition (lipids and metabolites) throughout the breastfeeding period.

In only women with FH, we will investigate

The concentration of statins in the breast milk and dried blood spot of the offspring of women with FH after start of lipid-lowering medication.The concentration of total cholesterol and metabolic markers in dried blood spots collected at 12 months postpartum in the offspring of women with FH.

### Study sample

#### Women with FH

We aim to recruit a total of 50 pregnant women with FH across three countries (Norway, the Netherlands and the Czech Republic). Inclusion criteria for women with FH are (1) age 18 years or older, (2) confirmed diagnosis of FH through genetic testing or clinical assessment based on the Dutch Lipid Clinic Network^2^, (3) singleton pregnancy in the third trimester and (4) a sufficient command of Norwegian, Dutch, Czech or English language. Pregnant women with FH or women with FH planning to become pregnant will be informed about the study via outpatient lipid clinics in Norway, the Netherlands and the Czech Republic. In addition, patients will be recruited through advertisements via applicable national patient organisations, colleague healthcare professionals in the three countries and via social media platforms.

#### Women without hypercholesterolaemia (control group)

In Norway, 20 pregnant women will be included in a control group. Inclusion criteria for women without hypercholesterolaemia are (1) age 18 years or older, (2) singleton pregnancy in the third trimester and (3) a sufficient command of the Norwegian or English language. Exclusion criteria for the control group are (1) known pre-pregnancy hypercholesterolaemia, (2) a history of ASCVD, (3) pre-eclampsia or gestational diabetes and (4) pre-pregnancy body mass index (BMI) <18 or >30 kg/m^2^. The women in the control group will be recruited via advertisements on social media and via the University of Oslo and Oslo University Hospital.

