**Trial registration number:**

NCT05367310.

STRENGTHS AND LIMITATIONS OF THIS STUDYA strength of the study is the use of repeated measurements to enable close monitoring of the lipid level variations in women with and without familial hypercholesterolaemia (FH) during the first year postpartum.Another strength is the well-characterised FH diagnosis, which is genetically verified (for most of the participants) or clinically diagnosed.A limitation of the study is the small sample size, reflecting the limited availability of pregnant women with FH within the timeframe of this study.The absence of control group in two of the three countries is a limitation.Variability in breastfeeding practices (frequency, duration) is another limitation that may influence the lipid levels in the first year postpartum.

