### Primary outcome

In women with FH compared with women without hypercholesterolaemia, we will investigate

The change in serum lipid profile (total cholesterol, LDL-C, high-density lipoprotein cholesterol (HDL-C), triglycerides, lipoprotein(a)) from 2 to 4 weeks post partum up to 12 months postpartum (absolute and relative change).

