### Statistical analysis

Descriptive data will be expressed as mean (SD), median (IQR or min-max) or frequency (percentage). Mixed models for repeated measurements will be used to study the changes over time within and between the two groups. Missing data will be described, and mixed models for repeated measurements handle missing data.^19^ Potential confounding variables will be evaluated by directed acyclic graphs and included in the model. Depending on the amount of missing data in the confounding variables, multiple imputation will be considered.

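### Controls are screened for pre-eclampsia, gestational diabetes, BMI and ASCVD but FH women are not, so the FH-control contrast in change can mix FH with metabolic and pregnancy health unless it is restricted or modelled by visit

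*Protocol article*

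**What the plan says.** Under Study sample, the control group has four exclusions. Three are in this sentence: "Exclusion criteria for the control group are (1) known pre-pregnancy hypercholesterolaemia, (2) a history of ASCVD, (3) pre-eclampsia or gestational diabetes". The fourth is "4) pre-pregnancy body mass index (BMI) <18 or >30" kg/m².

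The FH group has inclusion criteria only: "Inclusion criteria for women with FH are (1) age 18 years or older, (2) confirmed diagnosis of FH through genetic testing or clinical assessment", plus a singleton third-trimester pregnancy and language. No limit on BMI, pregnancy complications or ASCVD is listed.

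The Primary outcome section sets these two groups against each other ("In women with FH compared with women without hypercholesterolaemia, we will investigate") for change in the lipid profile. The Secondary outcomes section uses the same framing for the association of breastfeeding with "additional markers for ASCVD risk", naming CRP, glucose and weight.

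For confounding, the Statistical analysis section says: "Potential confounding variables will be evaluated by directed acyclic graphs and included in the model". The analysis is a mixed model for repeated measurements. The limitations box names one imbalance between the groups, "The absence of control group in two of the three countries is a limitation", but not the difference in eligibility.

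**The concern.** Excluding hypercholesterolaemia from the control group defines the contrast and is not a fault. The other exclusions are different. Obesity, gestational diabetes and pre-eclampsia plausibly affect how triglycerides, HDL-C, glucose, CRP and weight move in the first year after delivery, and may affect breastfeeding itself. They can occur among FH women and, at entry, cannot occur among controls. A difference in change between the groups would be read as an effect of FH, although part of it could come from this one-sided screening.

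The stated remedy is to put confounders in the model. In a repeated-measures model, how they enter decides whether anything is corrected. The natural reading, a covariate added to the model, leaves the quantity of interest, group-by-time, essentially untouched.

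**Working it through.** **1. The plan's own figure.** Inputs from Sample size calculation: difference in change 0.8 mmol/L, SD 1.0 mmol/L in each group, 5% level (taken as two-sided), 80% power, ratio 2.5.

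Controls needed = (1 + 1/2.5) × ((1.960 + 0.842)/0.8)² = 1.4 × 12.26 = 17.17, rounded up to 18. FH women = 2.5 × 18 = 45. The stated 45 and 18 reproduce. Power from the noncentral t distribution is 0.806 at 45/18 and 0.846 at the planned 50/20. The eligibility difference does not affect this arithmetic; it is a matter of bias.

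**2. Size of the shift.** Let a share *f* of FH women have a condition that would exclude a control, and let their mean change differ by *d* from that of other FH women. The unadjusted group contrast in change then shifts by *f* × *d*. The documents give neither quantity. Assumed ranges:

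| *f* | *d* = 0.25 | *d* = 0.5 | *d* = 1.0 mmol/L |
|---|---|---|---|
| 10% | 0.025 | 0.05 | 0.10 |
| 20% | 0.05 | 0.10 | 0.20 |
| 30% | 0.075 | 0.15 | 0.30 |
| 40% | 0.10 | 0.20 | 0.40 |

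Relative to 0.8 mmol/L this runs from 0.025/0.8 = 3% to 0.40/0.8 = 50%.

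**3. What a main-effect covariate does.** Take two visits, group *g*, visit *t*, and a condition indicator *c* that is 1 only in affected FH women. With terms for *g*, *t*, *g* × *t* and *c*, and with complete visits, the fitted group-by-time coefficient is

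[(FH mean at visit 2 − γ*f*) − (FH mean at visit 1 − γ*f*)] − (control change),

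where γ is the coefficient of *c*. The two γ*f* terms cancel, so the result equals the unadjusted contrast and the whole shift *f* × *d* remains. With missing visits the cancellation is no longer exact, but a main effect still cannot describe a different change over time.

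**4. What a condition-by-visit term does.** Adding *c* × *t* gives affected FH women their own change. The group-by-time coefficient becomes unaffected FH women minus controls, which is the restricted contrast.

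Example: 50 FH women, 13 affected (*f* = 0.26), *d* = 1.0, true contrast 0.8. The expected unadjusted contrast is 0.8 + 0.26 = 1.06. The main-effect model also expects 1.06; the restricted contrast and the condition-by-visit model both expect 0.80. Averages over 60 simulated data sets (50/20, two complete visits, SD of change 1.0) were 1.055, 1.055, 0.795 and 0.795 in that order.

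**5. BMI.** Controls span 18-30 only. A BMI slope (by visit) fitted in the model is applied beyond 30 or below 18 with no control data there, so adjustment in that range rests on the assumed shape.

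**6. Cost of restriction.** Noncentral t, two-sided 5%, difference 0.8, SD 1.0:

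| FH women / controls | Power |
|---|---|
| 50 / 20 | 0.846 |
| 40 / 20 (20% removed) | 0.819 |
| 35 / 20 (30% removed) | 0.800 |
| 30 / 20 (40% removed) | 0.775 |
| 45 / 18 | 0.806 |
| 36 / 18 (20% of 45 removed) | 0.776 |
| 31 / 18 (30% of 45 removed) | 0.753 |

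A Norway-only contrast with 20-30 FH women (assumed; the count is not given) and 20 controls has power 0.693-0.775.

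**The case against.** The strongest reply is that adjustment already does the job. For a yes/no condition present only in FH women, its coefficient is estimated within FH, and the group coefficient is then exactly unaffected FH women minus controls. With one outcome per woman this holds: in a simulated 50/20 data set with 13 affected, the crude contrast was 1.202 and both the adjusted and the restricted contrasts were 0.873. This stands, and it rules out an inference a reader might draw, that covariate adjustment cannot remove the problem. It can for the yes/no conditions, provided the term is crossed with visit. The protocol article does not say that it will be.

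Other replies, and what stands of them:

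- *Stable differences in level cancel in absolute change.* True. Only differences in the course over time matter, and for LDL-C, the outcome behind the sample size, no effect is shown. A reader might infer that the LDL-C result is biased by a known amount; the documents support no figure.
- *The secondary markers are framed as associations with breastfeeding, not as simple group differences.* True, but those associations are still compared between the two groups.
- *ASCVD can result from FH.* True. The Introduction ties lifelong cholesterol burden to ASCVD risk, so removing these women changes the question. ASCVD should be handled separately.
- *Country.* The authors acknowledge this, and Norwegian FH women are recruited, so overlap exists. It is not a new fault.
- *A restricted analysis may be left to the analysis plan.* Fair as to detail, and such an analysis may exist there. The point rests on the eligibility rules, which the article does state.
- *Entry is at gestational week 36, so a control could still develop pre-eclampsia.* True; the separation holds at entry.

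**Conclusion.** The concern holds in a limited form. The eligibility rules differ between the compared groups on conditions plausibly related to the outcomes, and nothing else in the protocol article repairs this. If those conditions enter only as main effects, the group-by-time contrast keeps essentially all of the shift. For BMI outside 18-30, adjustment extrapolates.

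The size is unknown. The 0.025-0.40 mmol/L range rests entirely on assumed values of *f* and *d*. Triglycerides, HDL-C, glucose, CRP and weight are the outcomes most plausibly affected. Within BMI 18-30 and without the listed conditions the groups overlap, and ordinary adjustment can work there.

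A reader might also infer that the restricted comparison must replace the full-group one. That does not follow: starting from the calculated 45 and 18, restriction takes power below the 80% target, and the sponsor considers more than 50 FH women and 20 controls unrealistic. This is a cheap improvement to the analysis, not a defect that invalidates the design.

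**What to change.** - Pre-specify an FH-control comparison limited to FH women who meet the control criteria on pre-eclampsia, gestational diabetes and pre-pregnancy BMI, and report it beside the full-group comparison. Add exclusion of ASCVD history as a further variant.
- Equivalently for the yes/no conditions, include condition-by-visit terms. A single indicator for having any of them, crossed with visit, reproduces the restriction on those conditions exactly with complete visits; several separate indicators do so only approximately when conditions coincide in the same woman.
- Keep all FH women for within-FH trajectories.
- Add a Norway-only contrast as a sensitivity analysis for the acknowledged country imbalance.
- Mention the difference in eligibility among the limitations.

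The cost is mainly wording. The section on medical history and clinical examinations already provides for medical history, history of the current pregnancy, complications and BMI. Check that pre-pregnancy weight is recorded for FH women, since BMI at week 36 is not a substitute. The restricted comparison loses about 3-5 percentage points of power if 20-30% of FH women are removed (assumed): 0.846 to 0.80-0.82 with 50 and 20 enrolled, or 0.806 to about 0.75-0.78 starting from 45 and 18.

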### Study design and setting

The study will be a prospective study carried out in Norway, the Netherlands and the Czech Republic. The women will be included at 36 weeks gestation until 12 months post partum or to the end of the breastfeeding period if the participant is breastfeeding for more than 12 months. The study inclusion started in June 2022, with recruitment planned to conclude by the second quarter half of 2025. The data collection phase will end when the last participant has completed all applicable study visits, estimated to be by the end of 2026.

#### Study visits

Women are included in gestational week 36 (V0) and followed up at the main study visits (figure 1) scheduled at 2–4 weeks postpartum (V1), and 3 (V3), 6 (V6), 9 (V9) and 12 (V12) months postpartum and 1 (VE1) and 2 months (VE2) after the end of breastfeeding. At all these main study visits, a non-fasting venous blood sample, breast milk samples (for as long as breastfeeding) and information on health, diet and medical factors are collected (table 1). At additional study visits among the women with FH, for as long as they are breastfeeding, blood samples will be collected at 2 (V2), 4 (V4), 5 (V5), 7 (V7), 8 (V8), 10 (V10) and 11 (V11) months postpartum. These blood samples can be collected at a time of the women’s choice within the time window for the study visit at the blood drawing location at the hospital, laboratory or GP office. At the additional visits, information on breastfeeding status and maternal weight will also be collected.

**Figure 1 F1:**
[figure not shown]
Study design. FH, familial hypercholesterolaemia.

**Table 1 T1:** Data collection at study visits

Study visit (months)	Medical history, lifestyle factors	Breastfeeding status Maternal weight	Blood pressure	Dietary data	Offspring weight and length	Blood sample, routine measurements	Blood sample, additional measurements	Breast milk sample
**V0 (−1)**	X	X	X	X		X	X	
**V1 (1)**		X	X	X	X	X	X	X
V2 (2)		X				X		
**V3 (3)**		X	X	X	X	X	X	X
V4 (4)		X				X		
V5 (5)		X				X		
**V6 (6)**		X	X	X	X	X	X	X
V7 (7)		X				X		
V8 (8)		X				X		
**V9 (9)**		X	X	X	X	X	X	X
V10 (10)		X				X		
V11 (11)		X				X		
**V12 (12)**		X	X	X	X	X	X	X
VE0								
**VE1 (+1)**		X	X	X		X	X	X
**VE2 (+2)**		X	X	X		X	X	X

**Main study visits** (FH and controls): V0, V1, V3, V6, V9, V12, VE1, VE2.

Additional study visits (FH, for as long as breastfeeding): V2, V4, V5, V7, V8, V10, V11, VE0.

FH, familial hypercholesterolaemia.

In Norway, study visits will take place at the University of Oslo and at the outpatient lipid clinics in Trondheim, Bergen and Bodø. To increase participation from women living outside the larger cities in Norway, women will also be followed at digital study visits with blood samples collected at their local GP office. In the Netherlands, all study visits and blood sampling will be performed at the Erasmus University Medical Center in Rotterdam. In the Czech Republic, study visits will take place at four study centres in Prague, Brno, Hradec Kralove and Zlin.

### Outcomes

#### Medical history, lifestyle factors and clinical examinations

At the first study visit, information on medical history, including FH diagnosis (age, genetic/clinical), lipid-lowering treatment history, untreated lipid levels prior to pregnancy, use of other medication and dietary supplements, history of current and previous pregnancies, lifestyle factors (physical activity, diet and smoking) and education level, will be collected. At all main study visits (table 1), information on delivery and any complications during pregnancy or delivery, breastfeeding status (yes/no, exclusive/partial, and frequency), BMI and blood pressure are collected. Dietary data are collected at the end of pregnancy and 12 months post partum using a digital food frequency questionnaire to capture the habitual diet during pregnancy and breastfeeding. Dietary data are also collected at all main study visits using a 24-hour dietary recall interview or questionnaire to capture detailed information on the diet the days prior to the blood sample. Weight and length of the child will be collected at the main study visits. At the additional visits, breastfeeding status and frequency, and self-reported maternal weight will also be collected (table 1).

#### Blood samples

A non-fasting venous blood sample will be collected at the main visits and additional visits for as long as the women are breastfeeding (table 1). The following measurements will be performed: lipid levels (total cholesterol, LDL-C, HDL-C, triglycerides, apolipoprotein A1, apolipoprotein B, lipoprotein(a)), glucose, HbA1c, c-peptide, creatinine, albumin, alanine transaminase, aspartate transaminase, thyroid-stimulating hormone, free T4, white blood cell count, high-sensitivity CRP (hs-CRP), haemoglobin, ferritin, vitamin D, folate, vitamin B_12_ and fatty acid composition. At the main study visits, the following measurements will also be performed: (1) targeted serum metabolomic profiling, including lipoprotein profiling, amino acids and glucose metabolites; (2) circulating inflammatory markers (such as CRP, interleukin (IL)-6, IL-10, tumour necrosis factor-α and interferon-γ); (3) in the Oslo and Rotterdam study centres only: PBMC gene expression of inflammatory and lipid-related genes in order to identify the differences in metabolic pathways influenced by breastfeeding. Non-fasting blood samples are used to minimise the burden for the participants in this study as these measures show minimal changes in response to normal food intake.^15 16^

#### Breast milk samples

Breast milk samples will be collected at the main study visits (table 1) for as long as the women are breastfeeding. Main outcome measures in the breast milk samples are lipid profiling (lipidomics) and metabolite profiling (metabolomics).

If the women with FH (re)-start lipid-lowering treatment (eg, statin) while still having breast milk production, additional breast milk samples will be collected. This breast milk sampling will be standardised by collecting the breast milk samples on days 0, 1, 2 and 3 after statin initiation. For day 0, 1 and 2, a single breast milk sample is collected between 06:00-12:00. On day 3, when the statin is expected to have reached a steady state in breast milk, multiple breast milk samples will be collected at 0, 2, 5 and 12 hours after intake of the statin pill. For all breast milk samples, the participants are asked to pump one breast from full to empty. The concentration of statins will be measured in these breast milk samples. We expect to collect fewer breast milk samples from this time point as it may be challenging to synchronise the initiation of lipid-lowering treatment with the end of breastfeeding.

#### Dried blood spot samples

A dried blood spot sample (DBS) from the offspring of women with FH will be collected at 12 months postpartum if informed consent has been given. Lipid profile and other metabolic markers (eg, inflammatory markers) will be analysed in the DBS of the offspring to assess associations with maternal levels. Additionally, we will investigate the association between offspring lipid levels and other metabolic markers with the duration of breastfeeding, as well as the composition of breast milk.

If breast milk samples are collected at the start of lipid-lowering treatment, the women with FH will also be invited to take a DBS of themselves and their child (provided that informed consent has been given) to measure the concentration of the lipid-lowering drug in the DBS samples.

### Safety plan

A 30–50% increase in cholesterol levels during pregnancy is normal and expected, but there is limited knowledge available about when and how fast the cholesterol levels decrease after delivery. Women are not routinely monitored during the breastfeeding period. Therefore, the GP or treating physician at a lipid clinic of the women with FH will be informed about the participant’s lipid levels (total cholesterol, LDL-C, HDL-C and triglycerides) from the blood sample taken at 9 months postpartum (V9) to ensure that the GP or treating physician will evaluate further treatment for the woman.

### Sample size calculation

Sample size calculation for comparing the difference between the two groups (women with FH and control women without hypercholesterolaemia) in changes from 2 to 4 weeks to 6 months postpartum was performed for LDL-C (mmol/L) with 5% significance level and 80% power. Based on the experiences from previous studies, availability of pregnant women and motivation to participate, the project group does not find it realistic to include more than 50 women with FH and 20 control women, that is, a ratio of 2.5 between the sample sizes.

Amundsen *et al*^6^ studied changes during pregnancy in women with FH (n=22) and women without hypercholesterolaemia (n=149). Mean LDL-C in gestational week 36 in the two groups was 8.6 and 3.9, mmol/L, respectively. In the women with FH, mean LDL-C at 3–6 months post partum was 7.0 (n=17), that is, mean change of 1.6 mmol/L, but no information was given about postpartum LDL-C values in the women without hypercholesterolaemia. Fahraeus *et al*^17^ observed LDL-C at 2 months postpartum in healthy women (n=14) and the mean was 3.51 mmol/L. However, we are not aware of the results in the literature reporting SDs for the changes in LDL-C during breastfeeding for both women with and without FH.

A difference in LDL-C of 0.43 mmol/L (16.7 mg/dL) was shown to be associated with reduced occurrence of coronary heart disease in the IMPROVE-IT study.^18^ Thus, we consider a difference in LDL-C of 0.8 mmol/L to be a clinically relevant difference between the two groups (women with FH and control women) in changes from 2 to 4 weeks to 6 months postpartum. With a 5% level of significance, 80% power and a 2.5 ratio in sample size, we need 45 women with FH and 18 control women to observe a difference in changes of 0.8 mmol/L assuming an SD of 1.0 mmol/L in each group. Thus, we will include 50 women with FH and 20 control women.

